### Data monitoring and management

All quantitative data will be collected using the online secure data management system Castor EDC. Of eligible non-consenting patients the reason for non-participation will be collected. The qualitative data from focus groups and interviews will be audio-recorded and transcribed verbatim. The transcripts will be pseudonymized. All data, both study and meta data, will be stored in a secured, digital data safe in either the Maastricht University Medical Center for 25 years (data from the pilocarpine study) or the Leiden University Medical Center for 15 years (data from the MEP study).

### Data analysis

#### Analysis of effect evaluation

All analyses will be carried out using statistical software that supports multi-level mixed model analyses, including the latest version of IMB SPSS Statistics. Demographic and baseline disease characteristic data will be summarized for each treatment group by presenting descriptive statistics. For continuous variables, we will use the mean and standard deviation (SD) in case of a normal distribution, or median and first and third quartile in case of skewed distribution. In case of missing data, we will use stochastic regression imputation to produce a synthetic part of the data to allow for an intention to treat analysis that includes all patients. For all analyses on primary and secondary outcomes a *p* value < 0.05 will be considered to indicate statistical significance. However, interpretation of these significant results will primarily focus on clinical relevance.

The primary outcome (percentage responders at 4 weeks) will be computed by using multi-level logistic regression analysis in the MEP study due to its cluster design, and linear regression analysis in the pilocarpine study taking the randomization stratification variable (sex) into account. Results will be expressed as odds ratio (OR) with a 95% confidence interval (CI).

All secondary outcome measures will be described in full using either mean and standard deviation median and interquartile range for continuous measures or count and proportion for categorical measures. Between-group differences in secondary outcomes at 4, 8, and 12 weeks (i.e., mean GOHAI-NL scores [33], mean PRFS scores [35], and patients’ Global Perceived Effect [37] dichotomized into success and no success) will be tested using multivariable generalized linear regression analysis with a link-function depending on the distribution of the variable (i.e. gaussian, or linear regression for continuous variables, binomial, or logistic regression for binary outcomes).

Cost-effectiveness analysis will be performed to examine both the costs and health outcomes of the interventions versus the control group, using the EQ-5D-5L [34], iMCQ [38] and factual costs of the medicine.

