#### MEP study

For this study, we expect the intervention group (patients who follow the MEP) to have at least 25% more responders (patients with clinically relevant less dry mouth at 4 weeks) than in the control group (patients who receive CAU). To test the null hypothesis (expected difference in responders at 4 weeks of 25%) with a power of 0.8, an alpha of 0.05 and an intra cluster coefficient of 0.10, we will need to include 181 patients which is obtained in 12 clusters (six hospitals and six nursing home clusters). Taking into account a 20% dropout rate at 4 weeks due to the frailty of our study population, 228 patients are needed. Each participating center is therefore expected to include 19 patients.

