### Limitations

This study does come with some methodological challenges. Recruitment difficulty and loss-to-follow-up due to frailty, deteriorating condition or death are specifically of concern with this palliative study population. By excluding terminally ill patients (life expectancy of 4 weeks or shorter), limiting the number of questionnaires (thus participation burden) and increasing the sample sizes, we hope to limit the impact of this concern.

However, recruitment is not only a concern within the patient population. The post-covid health care system is under great pressure in the Netherlands. Increased healthcare consumption paired with staffing problems due to high burn-out and other illness absence rates have led to increased work pressure and vice versa. This may impact health care professionals’ willingness to participate in the MEP study for which active participation and an additional time investment is needed. We attempt to address this pre-emptively by offering intensive and easily accessible support as well as a monetary stipend per included patient. As for the pilocarpine study, patients are provided with one-on-one instructions by the researchers to administer the drops themselves, to relieve their regular care team of potential extra tasks.

Regarding the cluster non-randomized design of the MEP study, a balance was sought between methodological strength and logistic constraint. A non-randomized design enables us to include care institutions more swiftly and easily (on a rolling basis) within a limited time frame, but may bring in some level of response bias. However, its cluster design limits the level of bias as it merely takes place on an organizational level, not on the patient or clinician level as with a patient-randomized trial.

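### Single stochastic regression imputation followed by ordinary p-values and confidence intervals ignores imputation uncertainty; how much this matters depends on an imputation model the article leaves open

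*Protocol article*

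**What the plan says.** The missing-data rule is one sentence in Analysis of effect evaluation, and it covers both studies: "In case of missing data, we will use stochastic regression imputation to produce a synthetic part of the data". Its stated purpose is "to allow for an intention to treat analysis that includes all patients". The next sentence applies one threshold to every primary and secondary outcome: p < 0.05 "will be considered to indicate statistical significance". The primary result is to be an odds ratio with a 95% confidence interval, from a multi-level logistic model in the MEP study. That section mentions no repeated imputations, pooling rule or variance correction, and it does not give the variables or levels of the imputation model.

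The two studies plan for different losses. The MEP sample-size section reads: "Taking into account a 20% dropout rate at 4 weeks due to the frailty of our study population", giving 228 patients. The pilocarpine sample-size section goes from 114 to 120. The Limitations section says that "loss-to-follow-up due to frailty, deteriorating condition or death are specifically of concern" in this population.

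**The concern.** Stochastic regression imputation replaces a missing value with a regression prediction plus one random residual. This keeps the spread of the completed data about right, but the later analysis cannot tell drawn values from observed ones. It credits the trial with the full sample size, although the missing patients supplied no outcome, and the draw adds noise of its own. The model-based standard error reflects neither.

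At stake are the width of the intervals and the size of the test on the responder endpoint at week 4. The outcomes at weeks 8 and 12 are exposed too, where cumulative loss cannot be smaller. In patients selected for limited life expectancy, some gaps will also be due to death. A rule with no exception, applied to all patients, leaves room for NRS scores or EQ-5D values to be generated for visits after death.

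**Working it through.** **Inputs from the article.** MEP: 181 evaluable patients, 12 clusters, 20% dropout, 228 patients at 19 per cluster, intracluster coefficient 0.10, alpha 0.05. Pilocarpine: 57 evaluable per group, SD 3.8, 120 patients in total. **Assumptions.** Two-sided tests (sidedness is not stated), outcomes missing completely at random, no true effect, and imputation R² varied because it is not given.

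**The plan's own figures.** MEP: 181 / 0.80 = 226.25, rounded up to 227; 12 × 19 = 228. Pilocarpine: a 2-point difference with SD 3.8 and 80% power gives 57 per group, and 114 / 0.95 = 120. Both reproduce, so the planned losses are 20% and 5%.

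**Independent patients, arm in the imputation model.** With missing fraction f, the ratio of true to reported variance is

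ratio = 1 + (1 − R²) × [f/(1 − f) + f],

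and type I error is 2 × [1 − Φ(1.96/√ratio)].

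- f = 0.20, R² = 0: ratio = 1 + 0.25 + 0.20 = 1.45; type I error 10.4%; standard error 17% too small.
- f = 0.20, R² = 0.5: ratio = 1 + 0.5 × 0.45 = 1.225; 7.7%; about 10% too small.
- f = 0.20, R² = 0.7: ratio = 1.135; 6.6%; 6% too small.
- f = 0.05, R² = 0: ratio = 1 + 0.0526 + 0.05 = 1.103; 6.2%; about 5% too small.
- f = 0.05, R² = 0.7: ratio = 1.031; 5.4%; 1.5% too small.

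Simulation of a binary outcome, with no predictor beyond arm and 60 or 114 patients per arm, gave 10.2–10.7% at 20% missing and 6.0–6.5% at 5% missing. Complete-case analysis of the same data stayed at about 5%.

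**Arm left out of the imputation model.** Type I error stays at about 5%. The imputed fifth of patients carries no treatment difference, however, so the expected effect shrinks by a factor of 1 − 0.20 = 0.8. A true 25-point difference in responders would be estimated at about 0.8 × 25 = 20 points.

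**The MEP design.** Simulation with 12 clusters of 19, intracluster coefficient 0.10 and 20% missing gave these type I errors:

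| Imputation uses | Cluster-level t-test: full data | Imputed | Random-intercept logistic model, likelihood-ratio test: full data | Imputed |
|---|---|---|---|---|
| Arm only | 5.2% | 10.9% | 7.3% | 14.1% |
| Cluster | 5.1% | 5.0% | 7.1% | 7.4% |
| Neither | 4.7% | 5.1% | 8.9% | 8.8% |

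The logistic runs used a 35% responder rate and 1,200 replicates, so near 7% the Monte Carlo standard error is √(0.07 × 0.93 / 1,200) ≈ 0.7 percentage points. The 7–9% with full data comes from having only 12 clusters and is not caused by imputation.

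The pattern has a simple explanation. Arm-only imputation pulls every cluster towards its arm mean. This shrinks the between-cluster spread on which the standard error rests, but does not make the arm means any more certain. When imputation is done within cluster, the added noise appears in that spread and is counted. When neither is used, the arm difference shrinks along with the spread, so the test keeps its size and the effect is diluted.

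**The case against.** The strongest reply is that the article does not fix the imputation model, and that under a sensible one the harm may be small. Week-0 NRS exists for everyone and week-2 NRS for those still in follow-up, so R² = 0 is pessimistic. In the MEP study, imputation that respects organisation adds no inflation in the simulations. In the pilocarpine study, 5% loss leaves little to distort. Stochastic imputation is also better than filling in the bare prediction. And a journal article may leave detail to an analysis plan that is not shown here.

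Much of this stands, and it limits the size of the point. It does not remove it: the article names a method, and that method carries no imputation uncertainty. An analysis plan that follows the sentence inherits the fault, and one that uses multiple imputation contradicts it.

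Three stronger readings are tempting, and the document does not support them.

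- **A reader might infer that type I error is 8–10% in this project.** That range needs independent patients, arm in the imputation model and low R². The 20% dropout it uses belongs to the clustered MEP study alone, where the answer can be lower or higher.
- **A reader might infer that the plan imputes outcomes after death and so miscalculates the cost-effectiveness results.** The article never says so. The missing-data rule does not mention death, the Limitations section names it only as a cause of loss, and patients with a life expectancy of 4 weeks or less are excluded. What can be said is that no exception is stated.
- **A reader might infer that the MEP imputation ignores organisation.** The article gives no levels for the imputation model either way.

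**Conclusion.** The point holds in a limited form. The stated method is a single imputation analysed with ordinary standard errors. Depending on whether arm is in the imputation model, it either understates uncertainty or dilutes the effect, apart from favourable cases such as within-cluster imputation in the MEP study. The possible consequence is material in the MEP study and slight in the pilocarpine study at its planned loss. The figures assume data missing completely at random, a null effect and the imputation models listed; none of those models is stated in the article. The 11–14% upper end comes from two different tests, and the 14% includes the excess that 12 clusters produce even with complete data. The handling of deaths is an ambiguity to close and does not depend on any of these figures.

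**What to change.** Replace the imputation sentence in Analysis of effect evaluation with multiple imputation pooled by Rubin's rules. Put arm, baseline NRS, the other observed NRS scores and related measures such as sXI-D and PRFS in the imputation model, and include organisation as a level in the MEP study. For continuous outcomes, a likelihood-based mixed model on the observed data is an alternative. The number of imputations can be left to the analysis plan.

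In the same paragraph, limit imputation to patients alive at the visit, so that no NRS or EQ-5D values are generated after death. State how deaths enter the responder analysis and the cost-effectiveness analysis. More than one approach is defensible; the choice should be fixed before the data are analysed.

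The cost is revised wording, a little more analysis work and slightly wider intervals. Design, recruitment and data collection are unaffected.

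### Missing outcomes are handled by stochastic regression imputation with no pooling or variance correction, so standard errors are too small and a borderline p value can depend on the random seed

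*Protocol article*

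**What the plan says.** The protocol article, under Analysis of effect evaluation, gives one rule for missing data in both studies: "we will use stochastic regression imputation to produce a synthetic part of the data to allow for an intention to treat analysis". It states no number of imputed data sets, pooling rule, variance correction or seed, and does not list the variables in the imputation model. The same paragraph sets the decision rule: "For all analyses on primary and secondary outcomes a *p* value < 0.05 will be considered to indicate statistical significance". The primary models are a multi-level logistic regression for the MEP study and a linear regression that accounts for sex for the pilocarpine study.

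On expected loss, the sample size section for the MEP study says "Taking into account a 20% dropout rate at 4 weeks due to the frailty of our study population, 228 patients are needed". The corresponding section for the pilocarpine study expects little loss and goes from 114 to 120 patients. The Limitations section adds: "Recruitment difficulty and loss-to-follow-up due to frailty, deteriorating condition or death are specifically of concern with this palliative study population".

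**The concern.** Stochastic regression imputation replaces each missing value by a regression prediction plus one random residual, which gives one completed data set. A regression fitted to that data set cannot tell synthetic values from real ones. Two things follow. The random residuals add noise to the estimated effect, and the model reports a standard error as if every patient had been observed. Reported precision goes up while actual precision goes down.

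At stake are the confidence interval and p value of every primary and secondary comparison in which values are imputed, all judged at 0.05. A near-threshold result could also change with the random seed.

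**Working it through.** **Inputs from the article.** MEP study: "with a power of 0.8, an alpha of 0.05 and an intra cluster coefficient of 0.10", 20% loss at week 4, 12 clusters of 19. Pilocarpine study: 57 per group enlarged to 60. NRS is measured at weeks 0, 2 and 4 (Table 2).

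**Assumptions not in the article.** Two-sided tests; data missing at random (the simulations made loss unrelated to outcome); predictors explaining a share R² = 0 to 0.5 of outcome variance; in the re-derived responder simulations, a 30% responder rate.

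**The plan's own figures.**
- MEP: 181/0.8 = 226.25, so 227; 12 × 19 = 228. Reproduced.
- Pilocarpine: with a 2-point difference, SD 3.8, two-sided 0.05 and 80% power, n = 2(1.960 + 0.842)² × 3.8²/2² = 56.7, so 57 per group. Reproduced. The allowance is (120 − 114)/120 = 5%.

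**Individual-level test, arm in the imputation model.** Let n be the patients in an arm, m the fraction missing and r = (1 − m)n the number observed. The completed-data mean has variance σ²[R²/n + (1 − R²)(1/r + (n − r)/n²)]. The model reports about σ²/n. So

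ratio = R² + (1 − R²)[1/(1 − m) + m], and type I error = 2[1 − Φ(1.96/√ratio)].

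| m | R² | ratio | √ratio | 1.96/√ratio | type I error |
|---|---|---|---|---|---|
| 0.20 | 0 | 1.250 + 0.200 = 1.450 | 1.204 | 1.628 | 10.4% |
| 0.20 | 0.25 | 0.25 + 0.75 × 1.450 = 1.338 | 1.157 | 1.695 | 9.0% |
| 0.20 | 0.50 | 0.50 + 0.50 × 1.450 = 1.225 | 1.107 | 1.771 | 7.7% |
| 0.05 | 0 | 1.053 + 0.050 = 1.103 | 1.050 | 1.867 | 6.2% |
| 0.05 | 0.25 | 0.25 + 0.75 × 1.103 = 1.077 | 1.038 | 1.889 | 5.9% |
| 0.05 | 0.50 | 0.50 + 0.50 × 1.103 = 1.051 | 1.025 | 1.912 | 5.6% |

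At 20% loss the reported interval is therefore 1/1.204 = 83% to 1/1.107 = 90% of the width that matches the estimate's true variability.

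**Simulation of the same test** (60 or 114 per arm, 8,000 runs). At 20% loss: 7.5-10.5% for a continuous outcome and 6.5-8.4% for a responder outcome, against 4.7-5.4% for complete cases. At 5% loss: 5.2-6.2%. Drawing responder status directly, with no predictors and 60 per arm, was slightly higher at 20% loss: 10.3-11.3%.

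**MEP study** (12 clusters of 19, intra-cluster correlation 0.10, 20% loss).

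| Test | Complete data | Complete cases | Imputation ignores organisation | Imputation includes organisation |
|---|---|---|---|---|
| Cluster means, t on 10 df (4,000 runs) | not run | 5.1-5.2% | 8.3-9.5% | 5.0% |
| Random-intercept logistic, Wald (about 1,550 runs) | 8.5-8.6% | 7.6-9.2% | 11.7-13.0% | 7.8-10.3% |

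The cluster-level test takes its standard error from the spread of the cluster means. Imputation around organisation-specific predictions leaves its noise in that spread, where the test sees it. Imputation around an arm-wide prediction pulls the cluster means together and hides part of it. The logistic Wald test is already above 5% on complete data because there are only 12 clusters, so not all of its excess comes from imputation.

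**Arm left out of the imputation model.** Type I error was 4.6-5.0%, but imputed values then carry no treatment contrast. With no predictors the expected difference shrinks by the factor 1 − m; at 20% loss the planned 25-point difference becomes 0.8 × 25 = 20 points.

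**Seed.** Fixed data sets with a median p of 0.03-0.07 were re-imputed with 200 seeds each. The 5th to 95th percentile of p was about 0.01-0.20 at 20% loss and 0.02-0.09 at 5% loss. About half of the seeds gave p < 0.05.

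**Pooling.** In a further simulation (4,000 runs per setting, continuous outcome), 20 imputed data sets pooled by Rubin's rules gave 4.9-5.1% at 20% loss, where single imputation gave 8.4-10.3%. At 5% loss the figures were 4.9% and 6.1%.

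**The case against.** The article never says in words that values are filled only once; this follows from the standard meaning of the method's name. A stochastic regression draw is also the building block of regression-based multiple imputation, and a condensed article may leave the number of data sets and the predictors to a fuller document. This objection is fair about the unstated details. It does not clear the sentence itself: a method is named, its usual meaning is single imputation, and nothing stated beside it corrects the standard errors.

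Four stronger readings are tempting, and the article does not support them.
- A reader might apply the 20% error rates to both studies. The 20% loss is stated for the MEP study only; the pilocarpine study allows 5%.
- A reader might assume that the MEP imputation ignores organisation. The article does not say so, and the inflation in the cluster-level test depends on it.
- A reader might see a conflict between enlarging 181 to 228 for dropout and then analysing all 228. There is none. Enlarging for loss and analysing everyone by intention to treat is routine, and would be equally true under multiple imputation.
- A reader might project heavier loss, and so larger errors, to weeks 8 and 12. The article gives no loss figure for those visits.

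**Conclusion.** The point holds as a stated method that understates uncertainty, and it should be fixed. Its size is conditional. With data missing at random and arm in the imputation model, an individual-level test at nominal 5% runs at about 6.5-10.5% at 20% loss, depending on predictor strength and on whether the NRS or responder status is imputed. At the pilocarpine study's own allowance it is about 5.5-6%, which is a small inflation.

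For the MEP study at 20% loss, a cluster-level test runs at about 8-9.5% if organisation is ignored and about 5% if it is included. Part of any excess in the planned multi-level logistic test comes from having few clusters. If arm is left out, the harm moves from the type I error to a diluted effect. Dependence on the seed is present in both studies and is much weaker at 5% loss.

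These figures do not cover loss that depends on the unseen outcome, which is possible given the deterioration and death named under Limitations.

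**What to change.** Replace the sentence on stochastic regression imputation with multiple imputation pooled by Rubin's rules. The imputation model should contain treatment arm, week-0 and week-2 NRS and, in the MEP study, organisation. Impute the week-4 NRS and then derive responder status from it. For the continuous outcomes measured repeatedly, a likelihood-based mixed model on all visits is an equal alternative that needs no imputation.

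The cost is one sentence and a little programming, with no new data. Averaging over many draws removes the added m term, leaving a variance ratio of R² + (1 − R²)/(1 − m). At 20% loss this is 1.25 with R² = 0 and 0.5 + 0.5 × 1.25 = 1.125 with R² = 0.5, so individual-level intervals become about 12% to 6% wider (√1.25 = 1.118, √1.125 = 1.061). At 5% loss with R² = 0 the ratio is 1.053 and the widening about 3%. The estimate itself becomes less variable than under a single draw, and its dependence on the seed becomes small.

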### Study population

#### Patients with dry mouth

In both studies, patients in the palliative phase of their disease with moderate to severe dry mouth symptoms will be invited to participate in the study. Eligibility is assessed using the following inclusion criteria: dry mouth severity ≥ 5 on a scale from 0 to 10 (NRS), a life-limiting condition or frailty [24], an age of 18 years or older and possible palliative care needs as measured by the surprise question [25]. In order to fulfill the surprise question, that is “Would you be surprised if the patient died within 12 months?”, the answer must be “No”. Patients with severe cognitive decline, with previous radiotherapy to the head-neck area and/or with Sjögren’s syndrome will be excluded. Patients with a life expectancy of ≤ 4 weeks will also be excluded due to the primary endpoint being set at 4 weeks. Lastly, in the pilocarpine study patients with mobility impairments impeding correct administration of the drops will be excluded.

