#### Primary outcomes

The primary outcome is the effectiveness of the intervention in reducing dry mouth complaints in patients with a life-limiting condition or frailty. This is measured by the percentage responders at week 4, for which a clinically relevant response is defined as at least a 2-point reduction on the 11-point numeric rating scale (NRS). The NRS is a frequently used instrument in both clinical practice and research settings to score symptom severity, such as for pain, nausea and sleep [31]. The NRS for dry mouth ranges from 0 = no dry mouth symptoms to 10 = worst possible dry mouth symptoms [1, 7].

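### Patients who die before week 4 are imputed like any missing value and may count as responders, which raises responder percentages and can shift the odds ratio either way

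*Protocol article*

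**What the plan says.** The primary outcome of both studies is binary. Primary outcomes states: "This is measured by the percentage responders at week 4". A responder is a patient whose score falls by two or more points on the 0 to 10 scale.

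Analysis of effect evaluation sets one rule for missing data in both studies, stochastic regression imputation, and gives its purpose: "to allow for an intention to treat analysis that includes all patients". Results are to be odds ratios with 95% confidence intervals.

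Three other places bear on how many week-4 scores will be missing because the patient has died:

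- Limitations: "loss-to-follow-up due to frailty, deteriorating condition or death are specifically of concern with this palliative study population".
- Sample size, MEP study: "Taking into account a 20% dropout rate at 4 weeks due to the frailty of our study population".
- Study population: inclusion requires the answer no to the question "Would you be surprised if the patient died within 12 months", while "Patients with a life expectancy of ≤ 4 weeks will also be excluded due to the primary endpoint being set at 4 weeks".

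The article nowhere separates death from other reasons for a missing score, and it does not define response as being alive with the required reduction.

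**The concern.** A patient who dies in week 2 has no week-4 score. The value is not an unobserved measurement; it does not exist. The stated rule nevertheless creates one, because every patient must enter the analysis and no exception is made. If the synthetic score lies two or more points below baseline, the patient is counted as a treatment success.

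Two things are at stake. The first is the reported responder percentage in each arm, which will include patients who died. The second is the comparison between arms. If early deaths differ between arms, the rule hides that difference inside imputed scores. In the MEP study, organisations are allocated in order of sign-up and not at random, so a difference in early mortality that has nothing to do with the programme is plausible.

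**Working it through.** **Inputs from the article.** MEP: 181 patients needed, 20% dropout at 4 weeks, 12 centres of 19, 114 per arm, 25 percentage points more responders expected. Pilocarpine: 114 needed, 120 planned, 60 per group.

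**Assumed, because the article does not give them.** A control response of 20%, hence 45% on MEP; death shares of 5% to 20% before week 4. The value 20% is a ceiling for MEP overall, since it treats every planned dropout as a death.

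**1. The plan's own figures.** 181 / (1 − 0.20) = 226.25, rounded up to 227; 12 × 19 = 228, as stated. Planned MEP loss is 0.20 × 228 = 45.6, about 46 patients, from all causes. Pilocarpine: 114 / 0.95 = 120, so the allowance is 6 / 120 = 5%.

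**2. Responder percentage.** Let p be the response rate among patients with data, d the share who die, and q the rate at which imputation makes the dead responders.

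- Imputed: p(1 − d) + qd
- Death as non-response: p(1 − d)
- Gap: qd, which is never negative and equals pd if the dead are imputed at their arm's rate.

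With p = q = 0.45, 5% deaths give 45% against 0.45 × 0.95 = 42.75%; 20% deaths give 45% against 0.45 × 0.80 = 36%.

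**3. Odds ratio, with arm in the imputation model.** The imputed analysis returns (0.45/0.55) / (0.20/0.80) = 3.27 whatever the deaths. With deaths as non-response:

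| Deaths, MEP v control | Responders, MEP v control | Odds ratio | Imputed 3.27 is |
|---|---|---|---|
| 5% v 5% | 0.4275 v 0.190 | 3.18 | higher |
| 10% v 10% | 0.405 v 0.180 | 3.10 | higher |
| 20% v 20% | 0.360 v 0.160 | 2.95 | higher |
| 20% v 10% | 0.360 v 0.180 | 2.56 | higher |
| 10% v 20% | 0.405 v 0.160 | 3.57 | lower |
| 5% v 15% | 0.4275 v 0.170 | 3.65 | lower |

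The pattern does not hang on the 20% control rate. With 50% v 25% response the imputed odds ratio is 3.00. Deaths of 15% on MEP and 25% on control give 0.50 × 0.85 = 0.425 and 0.25 × 0.75 = 0.1875, so (0.425/0.575) / (0.1875/0.8125) = 3.20.

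**4. Odds ratio, with arm left out of the imputation model.** Take 20% deaths in both arms. The pooled response among those with data is (0.36 + 0.16) / 1.6 = 0.325. The arms become 0.36 + 0.20 × 0.325 = 0.425 and 0.16 + 0.20 × 0.325 = 0.225, giving an odds ratio of 2.55. That is below the 2.95 obtained with deaths as non-response.

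**5. Patients involved.** MEP, with 5% deaths per arm: 114 × 0.05 × (0.45 + 0.20) = 3.7 deceased patients entered as responders. Pilocarpine, with 5% loss of which half are deaths and assumed response of 50% v 25%: 60 × 0.025 × (0.50 + 0.25) = 1.1.

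**The case against.** The strongest objections are these.

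- **A condensed article.** Handling of death is often left to the full protocol or analysis plan. This would settle the matter if the article were silent. It is not: it states a rule and the aim of including everyone, and that rule, followed literally, imputes the dead.
- **Few deaths are expected.** Patients with four weeks or less to live are excluded because of the week-4 endpoint. This reduces early deaths. It cannot remove them, since prognosis is an estimate, and the article still plans for 20% MEP dropout and still lists death. How many of those losses are deaths is unknown, and the share may well be low. This part stands, and it limits the size.
- **Imputation may use week-2 data.** Scores and functional status at week 2 could carry deterioration into the prediction, so the dead need not be imputed like the survivors. This stands too: q may be below p. The gap shrinks but does not reverse.
- **Counting death as non-response is a choice.** It is. Other treatments of death can be defended for a symptom outcome, but the plan has to make a choice, and this one suits a binary responder endpoint.

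A reader might infer that the rule overstates the treatment effect in both studies. The documents do not support that. With more deaths on control, or with arm left out of the imputation model, the odds ratio is understated. Nor should all 46 planned MEP losses be read as deaths, or the 20% figure carried over to the pilocarpine study, which expects little loss and allows about 5%.

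**Conclusion.** The concern holds in this form: the stated rule lets a patient who dies before week 4 count as a responder in the primary analysis of both studies.

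Relative to death as non-response, the responder percentage rises by up to about pd in any arm with deaths, if the dead are imputed at no more than their arm's response rate. At an assumed 5% deaths and 45% response that is 2.25 percentage points. At the 20% ceiling it would be 9 points.

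The direction of the effect on the odds ratio cannot be stated. With equal deaths and arm in the model the imputed value is modestly too high (3.27 against 3.18 to 2.95); in other plausible cases it is too low. Deaths by arm and the imputation model would decide it, and the article gives neither.

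The issue is worth correcting for MEP and likely minor for pilocarpine, where about one patient is affected under the scenario shown. All death shares and control response rates are assumptions. These figures take the responder percentage as the primary endpoint in both studies, as Primary outcomes states.

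**What to change.** In the primary responder analysis of both studies:

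1. Count death before the week-4 assessment as non-response.
2. Limit imputation to patients alive at week 4 whose score is missing.
3. Report deaths before week 4 by arm.
4. Add one sensitivity analysis in which every loss before week 4, for whatever reason, counts as non-response.

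The cost is a sentence or two in the analysis plan and one extra analysis. The date of death must be recorded for every patient who dies before the week-4 visit. Responder percentages will come out slightly lower. The sample size need not change for this reason alone unless the sponsor expects a material share of the planned dropout to be deaths.
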